### **3.2 Rationale and Purpose**

While there is some evidence to support the effectiveness of social determinants of health screening-and-referral interventions in addressing patients’ social and economic needs, the literature is limited by low-quality studies; non-experimental project designs; and assessments that focus on process, as opposed to ones that measure health outcomes, health care utilization, and cost. One randomized

controlled trial found that systematically screening and referring for social determinants during well child care visits led to the receipt of more community resources for families, however receipt of such services was overwhelmingly low – even in the intervention group. For example, only 15% of families were able to access affordable childcare; 11%, food assistance programs; and 8% employment or job training programs.

It is unknown whether screening for social determinants alone, without providing additional support, is sufficient to address the HRSN of adult patients with higher medical complexity and more intensive acute care utilization patterns. Further, many of these patients also face barriers to accessing services to address their HRSN. Some of the most common barriers to accessing healthcare services are financial problems, employment issues, child/adult care, and housing insecurity. Barriers to accessing social services are similar to barriers accessing health services and include lack of transportation, eligibility requirements, low literacy, limited English proficiency, and different cultural experiences and expectations. High utilizers, in particular, experience poor coordination across medical, behavioral, and social services providers.

Although THRIVE-Basic is an evidence-based screening-and-referral model, implementing universal THRIVE at BMC has demonstrated that providing resource referral guides is necessary, but insufficient, for patients with higher medical complexity and more intensive acute care utilization patterns, many of whom also face barriers in accessing services for HRSN. As the THRIVE-Basic model of care has been implemented in several BMC clinics, we have a strong picture of the burden of HRSN for intermediate risk BACO members receiving care at BMC. Our preliminary data demonstrate that intermediate risk adult BACO patients have a disproportionate burden of HRSN. In addition, we know this population requires help to solve barriers to accessing both health services and social services. This represents convincing evidence that a more robust model – our proposed THRIVE+ patient navigation services model – is necessary to increase connection to, and receipt of, these important resources to reduce the burden of HRSN, particularly among intermediate risk BACO patients who experience disproportionate HRSN.

Patient navigation has been identified as an effective intervention to decrease barriers to access healthcare services. Patient navigators perform different tasks to help patients access health care, including providing logistic support for barriers, emotional support, interpreter services, appointment scheduling, appointment reminders, information and answering questions regarding care, connections to support services, and guidance or accompaniment of patients to appointments.

To address these barriers, we have developed the THRIVE+ intervention, the underlying rationale of which is based on the tenets of patient navigation. Patient navigation is based on the principle that reducing logistic and psychological barriers to services is an efficient and effective mechanism to increase engagement with services. Navigation has been used successfully in domains of cancer and mental health care, we believe that navigation services – conducted by pharmacy liaisons trained as patient navigators – may be a cost-effective strategy to help intermediate-risk patients' access community services that address HRSN.

Our study will compare the effectiveness of THRIVE-Basic with a more robust model, THRIVE+, the intensity of which is matched to the HRSN-burden and healthcare utilization patterns of an intermediate risk group of BACO members. THRIVE+ includes a patient navigation intervention component. In traditional patient navigation programs, a lay person from the community guides individuals through the healthcare system to receive appropriate services. Navigation has been used successfully to improve

health outcomes in cancer prevention as well as in cancer and mental health care. For the present study, we will train pharmacy liaisons (pharmacy technicians or pharmacy interns with at least a high school degree and four years of pharmacy experience) to provide patient navigation services, in addition to providing medication adherence support and assistance resolving barriers to accessing medication via the Pharmacy Care Program. In an effort to avoid duplication of services we chose to deliver the patient navigation intervention via a pharmacy liaison trained in patient navigation, thereby increasing the potential for sustainability should the intervention prove effective. This specialized pharmacy liaison job description includes as one job function “addressing HRSN by connecting patients to resources available within BMC and within the community.”

The primary aim of this study is to determine whether screening for HRSN and providing tailored printed referral guides that direct patients to specific hospital and community-based resources and employing the services of a pharmacy liaison to promote medication adherence (“THRIVE-Basic”), relative to adding to THRIVE-Basic the assistance of a pharmacy liaison with training as a patient navigator who provides targeted navigation services aimed at connecting patients with appropriate community resources (THRIVE+), will reduce hospital admissions and emergency department visits among patients who are members of a Medicaid accountable care organization and receive primary care at a large urban safety-net hospital.

## **4 Objectives**

### **4.1 Study Objectives**

Our study objectives are as follows:

1. Effectiveness: Evaluate whether THRIVE+ demonstrates superior results in reduction of acute healthcare utilization compared to THRIVE-Basic usual care program.
2. Budget impact: Assess whether the THRIVE+ model reduces net costs by reducing acute health care utilization.
3. Implementation: Determine if THRIVE+ enhanced patient navigation component results in identifying and addressing a greater number of HRSN compared to the patient-reported HRSN on the THRIVE screening tool.

We will pursue a fourth study objective, patient experience and satisfaction, measured via client satisfaction questionnaires (CSQ-8). This will be detailed in a separate Exempt Category 2 IRB submission.

### **4.2 Study Outcome Measures**

#### **4.2.1 Primary Outcome Measures**

Our primary outcome measure is a composite measure of hospital admissions and ED visits at 12 months.

Each subject will have 12-months of follow-up. To satisfy requirements of our funder, we will report the primary and secondary outcomes for only the THRIVE+ intervention arm participants on a monthly basis.

#### 4.2.2 Secondary Outcome Measures

Secondary outcomes measures will be measured by:

1. Total number of all-cause ED visits;
2. Total number of all-cause 30-day ED revisits;
3. All-cause 30-day ED revisits rate;
4. Total number of all-cause discharges from IP;
5. Total number of all-cause 30-day IP readmissions;
6. All-cause 30-day IP readmission rate.

Intermediate measures will be measured by:

1. Number and proportion of patients to have identified HRSN;
2. Number and proportion of patients to receive referrals for their HRSN;
3. Number and proportion of patients to receive community-based services to meet their HRSN;
4. Connection to housing resources;
5. Connection to employment resources;
6. Connection to food;
7. Patient-level average of Proportion of Days Covered (PDC) for pharmaceutical prescriptions.

A budget impact analysis will be conducted to estimate the short-term expenditure changes and financial consequences of THRIVE+ compared to THRIVE-Basic, focusing on direct costs of implementation (staffing, resources, eligible intervention population size, etc.).

Post-hoc measures:

1. Social determinants of health services or referrals (e.g., food pantry referrals, food pantry visits, utilities shut-off protection letters).

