## **7 Study Subject Selection**

### **7.1 Subject Inclusion Criteria**

To be eligible to participate in the study, an individual must meet all of the following criteria:

1. Age 18-64 years;
2. Be within the 3rd to 10th percentile for healthcare utilization and cost among BACO membership at the time of enrollment into the clinical program; and
3. Attend a primary care visit with a PCP (nurse practitioner or physician) in a BMC GIM clinic.

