| Patients to receive services to meet their HRSN     | Action for Boston Community Development data                                                                                                       | Research     | Quarterly – All enrolled patients                                                                                                                                                      |
| Connection to housing resources                     | Action for Boston Community Development data                                                                                                       | Research     | Quarterly – All enrolled patients                                                                                                                                                      |
| Connection to employment resources                  | Action for Boston Community Development data                                                                                                       | Research     | Quarterly – All enrolled patients                                                                                                                                                      |
| Connection to food                                  | Action for Boston Community Development data                                                                                                       | Research     | Quarterly – All enrolled patients                                                                                                                                                      |
| Patient-level average of Proportion of Days Covered | BMC HealthNet Plan claims data                                                                                                                     | Routine Care | Quarterly – All enrolled patients                                                                                                                                                      |

|                                        |  |  |  |
|----------------------------------------|--|--|--|
| (PDC) for pharmaceutical prescriptions |  |  |  |
|----------------------------------------|--|--|--|

Table 2. Post-Hoc Measures

| Post-hoc measure                                     | Data Source                 | Data collected as part of Routine Care or for Research? | Measurement Time Points (Post-Enrollment) |

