|  | 
categorical variables. Due to a potential high number of patients with zero-count visits (136 out of 364, 37%), we employ a zero-inflated negative binomial model, which is a two-part model that examines simultaneously the odds of any visit, and the rates of visits among those patients who have any health care utilization. We use Bayesian Information Criteria as the model goodness-of-fit measure to compare zero-inflated negative binomial model with other models for the rates outcomes, including over-dispersed Poisson model, and negative binomial model. As a sensitivity analysis, we also model only the binary outcome of any utilization using logit link function. In the adjusted regression models, we will control for any factors including baseline utilization that are found statistically significant between the two arms. We report odds ratios and 95% CI for binary outcome (e.g., any visit) and rate ratios for the outcomes of inpatient and ED visits. We also compare the secondary outcomes of health-related social needs (e.g., connected to community-based partner; received services through referral to community partner; referrals and visits to hospital food pantry; received utility shutoff protection letter) between the two arms and examine adjusted intervention effect using logistic regression with odds ratio and 95% CI.
 
The primary analyses will be based on intent-to-treat. Because participants may receive varying “doses” of the intervention, we will also analyze the intervention effect according to whether participants received a minimum dose of the intervention. If the pharmacy liaison-patient navigator documents in their first telephone assessment that the patient has received the THRIVE screening in the past three months, and rescreens the patient if they have not been screened in the past three months, we consider the patient to have received the minimum intervention dose.
 |

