### **4.2 Participants' characteristics at inclusion**

Table 1 shows descriptive characteristics for the usual care and enhanced usual care groups. The usual care and enhanced usual care groups differed in the respective proportion who spoke English (78% vs. 87%), reported housing insecurity (9% vs. 13%), received a referral to the hospital food pantry in the past 12 months (14% vs. 25%), had at least one visit to hospital food pantry in past 12 months (12% vs. 20%) and had a diagnosis of PTSD (21% vs. 14%). The majority belonged to a racial/ethnic minority group, and 96% had received screening for health-related social needs in the past year. Approximately two-thirds of patients had significant medical comorbidity, and nearly half carried a diagnosis of depression.

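### Need-specific referral, service and connection outcomes should be adjusted for baseline need in the matching domain, not only when the arms differ significantly on it

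*Combined protocol and SAP*

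**What the plan says.** Protocol 4.2.2 includes among the intermediate measures "Number and proportion of patients to receive community-based services to meet their HRSN", a parallel measure for referrals, and items given by label only, such as "Connection to housing resources". Table 1 in protocol section 9 gives the timing of each as "Quarterly – All enrolled patients". Entry does not require a social need: besides age and utilization rank, the only inclusion criterion in 7.1 is "Attend a primary care visit with a PCP (nurse practitioner or physician) in a BMC GIM clinic".

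The SAP synopsis (Statistical method) will compare HRSN outcomes "between the two arms and examine adjusted intervention effect using logistic regression with odds ratio and 95% CI". It names connection to and services from the community partner, food pantry referrals and visits, and utility letters. The synopsis, SAP 5.1 and SAP 5.3.2 all limit the adjusted models to factors, baseline utilization included, on which the arms differ significantly. SAP 6.2 carries similar methods over to the secondary outcomes.

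SAP 4.2 lists baseline differences, usual care first, in per cent: "reported housing insecurity (9% vs. 13" and "received a referral to the hospital food pantry in the past 12 months (14% vs. 25". It also says that "96% had received screening for health-related social needs in the past year".

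Need is looked for differently by arm. Protocol sections 8 and 9 have the THRIVE+ navigator repeat the screener every three months. The control liaison does not screen systematically (protocol section 8; SAP synopsis), although control patients remain eligible for routine THRIVE screening at primary care visits.

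**The concern.** A patient is much more likely to be referred for, or connected to, housing help if there is a housing need. Baseline need in a domain is therefore a strong predictor of the outcome in that domain, and a chance imbalance in it passes almost directly into the comparison of arms. A rule that adjusts only after a significant baseline test protects poorly here. An imbalance can be too small to reach significance at this sample size and still be large relative to a rare outcome.

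The protocol's hypothesis (12.1) is that THRIVE+ raises connection to resources and thereby lowers acute utilization. These outcomes will be read as evidence on that mechanism. An odds ratio that partly reflects who entered with the need would be misread.

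**Working it through.** The plan gives no power, rate or effect size for these outcomes, so there is no figure to reproduce. The planned 364 (182 per arm) was set for the primary outcome. It is used below only as an assumed arm size, because the documents do not state the actual split.

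**Would the SAP rule pick up housing need?**
- Inputs (SAP 4.2): 9% and 13%. Counts: 0.09 × 182 ≈ 16 and 0.13 × 182 ≈ 24, so 40 of 364 in all.
- Pooled proportion 40/364 = 0.110. Difference 24/182 − 16/182 = 0.044. Standard error √(0.110 × 0.890 × 2/182) = 0.033. So z = 1.34 and p ≈ 0.18, or about 0.24 with continuity correction.
- Rounding does not change this. Counts of 16 or 17 round to 9% and counts of 23 or 24 round to 13%. Across those pairs the uncorrected p runs from 0.18 to 0.31. Housing need fails the rule in every case.

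**What would the unadjusted all-enrolled comparison show?** Let c be the probability of connection given baseline need and d the probability without it, both equal in the two arms.
- Proportion connected = need × c + (1 − need) × d.
- With d = 0 the ratio is 0.13c / 0.09c = 1.44 for any c. At c = 50% (assumed) the proportions are 4.5% and 6.5%. The odds ratio is 1.45 to 1.51 for c from 10% to 100%.
- With d above 0 the ratio shrinks. At c = 50% and d = 1% (assumed): (0.065 + 0.0087) / (0.045 + 0.0091) = 0.0737 / 0.0541 = 1.36. At d = 5%: (0.065 + 0.0435) / (0.045 + 0.0455) = 0.1085 / 0.0905 = 1.20.
- So 1.44 is the upper end, reached when connections arise only in patients with baseline need.

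**Does the rule treat the domains alike?** At the same arm sizes:

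| Baseline item | Usual care vs enhanced | p, uncorrected | p, corrected | Adjusted for? |
|---|---|---|---|---|
| Housing insecurity | 16 vs 24 | 0.18 | 0.24 | No |
| Pantry referral, past 12 months | 25 vs 46 | 0.005 | 0.008 | Yes |
| Pantry visit, past 12 months (12% vs 20%) | 22 vs 36 | 0.045 | 0.063 | Depends on the version of the test |

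Adjustment would thus vary from one outcome to the next according to the baseline p-value.

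**Size of a baseline-need subset.** For housing it is about 40 patients, or 20 per arm at 11%. With assumed connection of 25% vs 50%, power is about 37%. Across need of 9–13% and connection pairs of 15/30%, 25/50% and 30/60%, it is 17–55%. Such an analysis can supply estimates and intervals, not a test to rely on.

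**The case against.** Much of the case on the other side is right.

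- A reader might infer that these outcomes are impossible for the 87–91% without housing insecurity. The documents do not support that. The figure is the share who did not report it at inclusion, homelessness is a separate screener domain, and needs can arise or be disclosed over 12 months. No prevalence of employment or food need is given at all.
- A reader might infer that the plan has no denominator. Table 1's reference to all enrolled patients and the between-arm logistic model point to everyone enrolled. What is missing is an explicit statement of that, and of how a patient without the need is scored.
- A reader might infer that the comparison measures having or disclosing a need instead of being connected. It measures identification and connection together. Identifying needs is part of the intervention and of objective 3, so the all-enrolled comparison is legitimate.
- A reader might infer that an all-enrolled and an identified-need denominator would point in opposite directions. That takes an assumption such as 50% more needs found in THRIVE+ with no extra connections (30% / 1.5 = 20%, against 30%). Nothing in the documents supports that value.

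Two further points have weight. Protocol 12.3 and the SAP synopsis name screening results among potential confounders, and SAP 5.3.2 also allows covariates chosen in advance, so baseline need is not ruled out. But the examples are age and gender, the sentence concerns the primary outcome, and the rule repeated for adjusted models is the significance rule. Also, housing connection is a protocol measure that the SAP does not name, so the 1.44 illustrates the mechanism and is not a forecast for an SAP endpoint.

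**Conclusion.** The point holds as one about covariate adjustment. The significance rule would leave out a strong predictor of a need-specific outcome, and for housing the baseline imbalance alone could produce a ratio of up to about 1.44 in favour of THRIVE+. This rests on three assumptions: 182 per arm, equal connection given baseline need, and few connections among patients negative at baseline. The ratio falls to 1.36 or 1.20 if 1% or 5% of those patients are connected and c is 50%.

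A gap of 9% vs 13% is compatible with chance. It is an accidental imbalance that the analysis can remove, not a systematic fault in the measure. Moving to a denominator of needs identified during follow-up would make matters worse, since the frequency of systematic screening depends on arm. The primary utilization outcome and its sample size are untouched.

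**What to change.** 1. State in Table 1 and the SAP that all enrolled patients are the main denominator for each referral, service and connection outcome, and that a patient with no recorded connection is scored as no.
2. Adjust each need-specific outcome for baseline need in the matching domain, taken from the last THRIVE screen on or before enrolment, regardless of any baseline significance test.
3. Add a supportive analysis in patients positive for that domain at that screen, by the same rule in both arms, reported as estimates with confidence intervals.

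The cost is a few lines of SAP and Table 1 wording, using screening data already collected. The supportive set is small (about 40 patients for housing) and does not capture needs found later, so it cannot replace the all-enrolled result. The roughly 4% not screened in the past year need a missing category in step 2 and drop out of step 3. Some baseline screens may be up to a year old.

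One thing must be settled first. Table 1 implies that the partner organization's data cover everyone enrolled, whereas the text of protocol section 9 describes its check for intervention participants only. The comparison requires the same ascertainment in both arms.

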## 5 Study Design

### Design overview

We are performing a pragmatic trial of systematically screening for HRSN and providing a tailored set of printed referral guides that direct patients to specific hospital and community-based resources ("THRIVE-Basic"), relative to adding to THRIVE-Basic the assistance of pharmacy liaison-patient navigator, who provides targeted navigation services aimed at connecting patients with appropriate community resources (THRIVE+), to reduce hospital admissions and emergency department visits. Assignment to the study conditions is at the individual patient level. We will include adult patients age 18-64 receiving primary care in the General Internal Medicine Practice of Boston Medical Center who are members of the Boston Medical Center Medicaid ACO, and whose healthcare utilization ranks in the top 3-10% of the ACO membership. Because it is not practicable to obtain informed consent on all participants enrolled in the clinical program, we are requesting a waiver of informed consent for participants in both study arms. We are also requesting to obtain a waiver of HIPAA authorization. This will be justified in this protocol.

